## Abstract

**Background:**

Post-stroke shoulder pain (PSSP) is a frequent complication that significantly impedes upper limb rehabilitation in stroke patients and contributes to global healthcare costs amounting to billions of dollars each year. Beyond the financial impact, PSSP severely compromises patients’ quality of life. Developing effective treatments to reduce pain and improve shoulder joint function in individuals with PSSP remains a pressing clinical priority. We are currently conducting a rigorously structured randomized controlled trial to evaluate and compare the effectiveness of Discovery of Posture Secret (DPS) therapy and Standardized Chinese Tuina Therapy (SCTT) in stroke patients diagnosed with shoulder pain through musculoskeletal ultrasound. This paper presents the trial’s design and implementation.

**Methods/design:**

This is a single-center, 4-week randomized controlled trial carried out at the Department of Rehabilitation, Fuyong People’s Hospital, Bao’an District, Shenzhen, Guangdong Province. The objective is to assess the comparative effectiveness of DPS and SCTT in patients with PSSP. Eligible participants are stroke survivors aged between 40 and 60 years who meet the diagnostic criteria for PSSP established in China. Participants will be randomly assigned to one of two treatment groups, receiving one 40 min session each weekday (Monday through Friday) for four consecutive weeks, with rest on weekends. The primary outcome is the change in pain intensity measured by the Visual Analog Scale (VAS) at 2 weeks, 4 weeks, and at a 1-month follow-up. Secondary outcomes include shoulder joint function and general functional recovery at 4 weeks, evaluated using shoulder range of motion (ROM), the absolute difference in vertical distance between the medial superior angle of the scapula and the second thoracic spinous process, musculoskeletal ultrasound findings, and the Modified Barthel Index (MBI).

**Discussion:**

This is the first randomized trial to compare the effectiveness of DPS and SCTT in PSSP patients, with a one-month follow-up. We propose a carefully constructed randomized controlled trial that, for the first time, employs musculoskeletal ultrasound as an objective tool for assessing PSSP. This methodological advance aims to increase the objectivity and reliability of the outcome data. The results of this trial are expected to carry substantial public health relevance for the growing population affected by PSSP and may inform better treatment approaches and functional recovery strategies.

**Clinical trial registration:**

ClinicalTrials.gov, identifier NCT06763796.

## Introduction

PSSP is a common complication after stroke, characterized by pain in the shoulder region, typically on the hemiplegic side. It stems from both musculoskeletal and neurological dysfunctions and significantly hampers functional recovery (1). Clinically, PSSP presents with localized or referred pain, limited range of motion, muscle spasticity, and, in some cases, shoulder subluxation (2). Prevalence estimates vary widely, from 16 to 84% among stroke survivors, depending on diagnostic criteria and study populations (3). The condition often leads to prolonged hospitalization and imposes a heavy financial toll, contributing to billions in global healthcare expenditures annually, driven by direct medical costs and lost productivity (4). Clinical reports further suggest that PSSP affects not only postural stability and mobility but also delays recovery of hand function and complicates basic self-care tasks, increasing the caregiving and financial burden on families (5, 6). These factors point to an urgent need for effective treatments that can reduce pain and support rehabilitation progress.

Currently available therapies for PSSP face serious limitations in terms of efficacy, accessibility, and safety. Nonsteroidal anti-inflammatory drugs (NSAIDs), such as celecoxib, are frequently unsuitable for patients with cardiogenic stroke, particularly those who have undergone cardiac surgery, due to the elevated risk of serious cardiovascular thrombotic events, including myocardial infarction and stroke, especially in those with existing cardiovascular disease (7). Neural blockade, though potentially effective, requires ultrasound guidance and skilled practitioners, restricting its use to advanced healthcare settings (8). Physical therapy options like transcutaneous electrical nerve stimulation (TENS) and electroacupuncture contribute to pain control, but they carry risks for patients with implanted cardiac devices, such as pacemakers or defibrillators, owing to the danger of electromagnetic interference and device malfunction (9, 10). These challenges highlight the urgent demand for treatment strategies that are both low-risk and cost-effective, making this area a key focus in ongoing clinical research.

The DPS technique, developed by [name], a senior physical therapist from Korea with over two decades of clinical experience, and [name], Director of the Rehabilitation Medicine Department at Qingdao University Affiliated Hospital, introduces a novel joint movement method known as “shear motion.” This approach has demonstrated promising therapeutic effects in pain relief and neurorehabilitation (11–13). DPS begins with a structured postural assessment performed in the patient’s neutral stance to identify primary contributors to joint misalignment. Its foundation lies in the 4R technique: Resetting Joint Malalignment (RJM) corrects abnormal joint alignment; Resetting Abnormal Muscle Function (RAM) restores muscle performance; Resetting Joint Stabilization (RJS) re-establishes joint stability; and Resetting Sensory-Motor Control (RSMC) targets improvements in sensory and motor regulation. These combined interventions offer a multi-faceted strategy for correcting joint dysfunction and reestablishing functional movement.

In our clinical experience, supported by patient feedback, the DPS method has shown a clear capacity to reduce post-stroke shoulder pain, improve shoulder range of motion, and promote functional recovery of the hemiplegic limb. Encouraged by these observations, we have initiated a large-scale trial to assess the comparative effectiveness of DPS in patients experiencing symptomatic post-stroke shoulder pain. We hypothesize that DPS will demonstrate greater efficacy than SCTT. The goal of this study is to evaluate DPS as a potentially more effective treatment that not only reduces pain but also improves shoulder mobility and minimizes functional impairments that affect the quality of life in millions of stroke survivors with hemiplegia.

This paper outlines the design and protocol of the first randomized controlled trial directly comparing DPS with SCTT for managing post-stroke shoulder pain. The study aims to fill an important evidence gap and offer practical guidance for clinical treatment of this complex condition. Results will be published in compliance with the Consolidated Standards of Reporting Trials (CONSORT) guidelines (14), ensuring transparency and methodological soundness.

## Methods/design

### Study design overview

This study is a 4-week, single-center, single-blind randomized controlled trial. Over the next 3 years, 48 patients diagnosed with post-stroke shoulder pain will be randomly assigned to either the DPS group or the SCTT group. Both treatments will be delivered once daily from Monday to Friday (five sessions per week), with each session lasting 40 min, over a four-week period. Weekends will be reserved for rest. Figure 1 presents the study timeline and intervention phases.

**Figure 1 fig1:**
[figure not shown]
Study design flowchart: a detailed depiction of participant progression through each stage of the study.

The primary outcome is pain intensity, assessed using the VAS, a widely recognized and validated tool. VAS scores will be recorded at baseline, at 2 and 4 weeks during treatment, and again at a 1-month follow-up after completion of the intervention. Secondary outcomes assess shoulder joint function across four domains. First, ROM will be measured to evaluate mobility of the affected shoulder. Second, the absolute vertical distance difference between the medial superior angle of the scapula on the affected side and the second thoracic spinous process will be recorded. Third, musculoskeletal ultrasound will be used to assess five key indicators: presence of effusion around the long head of the biceps tendon sheath, calcification in the supraspinatus muscle, calcification at the insertion of the subscapularis tendon, subdeltoid bursa thickness (in millimeters), and the distance from the acromion to the greater tuberosity of the humerus. Lastly, the MBI will be used to evaluate overall independence in daily living activities. Covariates include age, sex, body mass index (BMI), stroke type (hemorrhagic or ischemic), and time since stroke onset. All outcome measures will be collected at baseline, 2 weeks, and 4 weeks after treatment begins. A follow-up VAS will be conducted 1 month post-intervention to assess the sustained effects of DPS in relieving post-stroke shoulder pain. The physical function assessments will be performed by trained evaluators blinded to treatment allocation, and data analysis will be conducted by statisticians also blinded to group assignments.

Detailed outcome variables and their classification as endpoints or intermediate measures are summarized in Table 1.

**Table 1 tab1:** Baseline assessment and sequence of trial measurements for primary and secondary outcomes.

	Before-intervention	Mid-intervention	Post-intervention	1-month follow-up
Time (weeks)	**0**	**2**	**4**	**8**
Baseline				
Sex (male/female)	**√**			
Type of stroke (ischemia/hemorrhage)	**√**			
Age, y	**√**			
BMI	**√**			
Time since stroke, y	**√**			
Primary outcome variable				
VAS	**√**	**√**	**√**	**√**
Secondary outcome variables				
Shoulder ROM				
Flexion (0–180°)	**√**	**√**	**√**	
Extension (0–50°)	**√**	**√**	**√**	
Abduction (0–180°)	**√**	**√**	**√**	
Adduction (0–40°)	**√**	**√**	**√**	
Internal rotation (0–70°)	**√**	**√**	**√**	
External rotation (0–90°)	**√**	**√**	**√**	
Horizontal abduction (0–45°)	**√**	**√**	**√**	
Horizontal adduction (0–135°)	**√**	**√**	**√**	
Absolute vertical distance difference: medial	**√**	**√**	**√**	
Superior scapula to T2 on affected side				
Musculoskeletal ultrasound				
Distance from the acromion to the greater tuberosity of the humerus	**√**	**√**	**√**	
Effusion of the long head of the biceps tendon	**√**	**√**	**√**	
Calcification of the supraspinatus muscle	**√**	**√**	**√**	
Calcification of the subscapularis muscle	**√**	**√**	**√**	
Thickness of the subdeltoid bursa	**√**	**√**	**√**	
Modified Barthel Index	**√**	**√**	**√**	

“√” Indicates that the corresponding outcome will be assessed at that time point.

The study will take place in the Rehabilitation Department of Fuyong People’s Hospital, Bao’an District, Shenzhen, Guangdong Province, China. Ethical approval was granted by the Institutional Review Board of Fuyong People’s Hospital, Bao’an District, Shenzhen.

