### Study sample

Participants will be eligible for inclusion if they meet all of the following criteria: (1) aged between 40 and 60 years; (2) diagnosed with a first-ever stroke (ischemic or hemorrhagic), confirmed by cranial CT or MRI; (3) onset of hemiplegic shoulder pain after the stroke, with a Visual Analog Scale (VAS) pain score ≥4; (4) Brunnstrom stage II to V on the affected limb; (5) no significant pre-existing shoulder disorders (e.g., rotator cuff tear, severe osteoarthritis, adhesive capsulitis) confirmed by ultrasound and clinical exam; (6) no severe cognitive impairment (Mini-Mental State Examination score ≥24); and (7) able and willing to provide written informed consent.

Participants will be excluded if they have: (1) subarachnoid hemorrhage; (2) two or more prior strokes; (3) significant shoulder subluxation (≥1 finger-width gap between acromion and humeral head) or flaccid paralysis; (4) clinical deterioration due to recurrent infarct or hemorrhage; (5) severe cardiopulmonary conditions (e.g., acute myocardial infarction, unstable angina, severe arrhythmia, aortic stenosis, pericarditis, malignant hypertension); and (6) other causes of shoulder pain unrelated to stroke, such as cervical spondylosis or referred visceral pain.

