### Enrollment and the informed consent process

Participants will be enrolled in groups of at least 10 per intervention cycle to support a structured group intervention setting and maintain an equal 1:1 allocation between the two treatment arms. Within 2 weeks prior to the intervention phase, baseline assessments will be conducted for 10 to 20 pre-screened individuals to establish an eligible pool for randomization.

Before any data are collected, the principal investigator (CW) or the research coordinator will initiate the informed consent process. Each participant will receive a written consent form and a detailed explanation of the study. Those who agree to participate will sign the form. Following consent, eligibility will be confirmed based on the predefined inclusion criteria. Once eligibility is verified, the study team will explain the trial procedures in detail to ensure that participants fully understand the nature of their involvement. Completion of these steps finalizes the enrollment process.

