### Randomization

Once written informed consent was obtained and baseline assessments were completed, an off-site research assistant performed the randomization using SPSS version 27. Participants were randomly assigned to either the DPS therapy group or the SCTT group. To reduce potential allocation bias, stratified randomization was applied based on time since stroke (in years) and stroke type (ischemic or hemorrhagic).

To ensure allocation concealment, all information regarding group assignment, therapy schedules, and intervention locations was communicated solely through centralized telephone contact, managed by the off-site research assistant. This method kept other study personnel blinded to group assignments and helped minimize bias throughout the intervention phase.

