### Data analysis

Statistical analyzes will be performed using SPSS version 27.0. All continuous variables will be tested for normality using the Shapiro–Wilk test. Normally distributed data will be expressed as mean ± standard deviation and analyzed using independent sample *t*-tests for between-group comparisons and repeated measures ANOVA for within-group comparisons across time points (baseline, week 2, week 4, and 1-month follow-up). Non-normally distributed data will be reported as medians with interquartile ranges and assessed using the Mann–Whitney U test and Friedman test, respectively. Categorical variables such as gender or stroke type will be analyzed using chi-square tests or Fisher’s exact tests when appropriate. A two-sided *p*-value < 0.05 will be considered statistically significant for all analyzes.

For musculoskeletal ultrasound outcomes, four key indicators will be analyzed: (1) distance from the acromion to the greater tuberosity of the humerus and (2) thickness of the subdeltoid bursa will be treated as continuous variables and analyzed using the same approach as other quantitative measures—independent *t*-tests or Mann–Whitney U tests for between-group comparisons, and repeated measures ANOVA or Friedman tests for within-group changes. (3) Calcifications in the supraspinatus tendon and (4) effusion around the long head of the biceps tendon sheath will be treated as binary variables (presence/absence) and compared between groups using chi-square tests. All ultrasound images will be independently reviewed by two experienced sonographers blinded to group allocation. Inter-rater reliability will be evaluated using Cohen’s kappa for categorical variables and intraclass correlation coefficients (ICC) for continuous variables. Any discrepancies will be resolved by consensus discussion.

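### Brunnstrom stage is determined for every patient at entry but is neither a listed baseline characteristic nor a covariate, so a chance motor imbalance would be only partly visible and not adjusted for in ROM and MBI

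*Protocol article*

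**What the plan says.** Under Study sample, inclusion criterion 4 is "Brunnstrom stage II to V on the affected limb". Stage therefore has to be established for every patient before entry. It appears nowhere else in the article.

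The Study design overview gives the covariate set: "Covariates include age, sex, body mass index (BMI), stroke type (hemorrhagic or ischemic), and time since stroke onset". The baseline block of Table 1 has rows for sex, stroke type, age, BMI and time since stroke, which are the same five.

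Under Randomization, "stratified randomization was applied based on time since stroke (in years) and stroke type (ischemic or hemorrhagic"); motor status is not a stratification factor.

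The Data analysis section assigns independent-sample t-tests (or Mann-Whitney U tests) "for between-group comparisons and repeated measures ANOVA for within-group comparisons across time points". No model with covariates is described, so even the five named covariates have no stated use.

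The trial size is given as "48 patients diagnosed with post-stroke shoulder pain will be randomly assigned", with the aim to "maintain an equal 1:1 allocation between the two treatment arms". Shoulder ROM in eight directions and MBI are secondary outcomes, each measured at baseline, week 2 and week 4 (Tables 1 and 2).

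**The concern.** Stages II to V span a wide range of motor recovery. Motor status is a plausible predictor of shoulder range and of independence in self-care, the subjects of two of the secondary outcomes. The article itself points this way: its section on the scapula-T2 distance attributes scapular malalignment to post-stroke weakness or spasticity. The DPS regimen also asks for active trunk movements and holds, so motor status may affect how fully it can be carried out.

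The article fixes a covariate set and a baseline schedule, and both leave out the one direct grading of motor impairment that the trial must already obtain. In arms this small, two things are at stake. If the arms happen to differ in stage, a reader of the ROM and MBI results cannot readily separate that difference from the treatment effect. And variation in outcome that stage could explain stays in the error term.

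**Working it through.** **Arm size.** Inputs from Sample size calculation: d = 0.91, alpha 0.05 (two-sided, from Data analysis), power 0.80, dropout 20%. Normal approximation: n = 2(1.96 + 0.842)²/0.91² = 18.96, so 19 per group and 38 in total. 38/0.80 = 47.5, which rounds up to 48, or 24 per arm. The plan's figures reproduce. (The exact two-sided t-test needs 20 per group; this does not affect the point.)

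**Chance of imbalance, stage split II-III versus IV-V.** The article gives no distribution of stage, so the number K of stage II-III patients among the 48 is an assumption. With 24 per arm and no stratification on stage, the number X in one arm is hypergeometric (48, K, 24), and the gap between arms is |2X − K|.

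| K (share of 48) | P(gap ≥ 4) | P(gap ≥ 6) |
|---|---|---|
| 24 (50%) | 0.387 | 0.148 |
| 19 (40%) | 0.24 | 0.08 |
| 14 (29%) | 0.34 | 0.11 |

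For K = 24, P(gap ≥ 4) is 1 − P(X = 11, 12 or 13) = 1 − (0.193 + 0.227 + 0.193) = 0.387. A gap of 4 is 4/24 = 17 percentage points and a gap of 6 is 25 points. For K = 19 the gap can only be odd, so those entries are for gaps of at least 5 and at least 7.

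**The same on a continuous scale.** The standard error of a standardised baseline difference is √(2/24) = 0.289. The probability of an imbalance of at least 0.3 SD is 30%, and of at least 0.5 SD is 8.3%.

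**What an imbalance would do.** Suppose the arms differ by 0.5 SD in stage and stage has correlation r with the outcome (r is assumed). The unadjusted difference shifts by 0.5r: 0.15, 0.25 or 0.35 outcome SD at r = 0.3, 0.5 or 0.7. Given that imbalance, the type I error of the unadjusted test is 1 − Φ((1.96 × 0.289 − 0.5r)/(0.289√(1 − r²))) plus the opposite tail, which comes to about 7%, 10% or 15%. Averaged over all randomisations it remains 5%.

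**Precision.** If stage explains a share R² of the residual outcome variance, adjustment multiplies the standard error by √(1 − R²).

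| Assumed R² | SE factor | SE reduction |
|---|---|---|
| 0.1 | 0.949 | 5% |
| 0.2 | 0.894 | 11% |
| 0.4 | 0.775 | 23% |

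The R² that matters is what stage adds once the baseline value of ROM or MBI is already in the model. The article gives no figure from which to estimate it, and it may be below any of these values.

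**The case against.** The strongest reply is that nothing here is contradictory. A choice of covariates can be left to a fuller plan, and the covariate sentence is not worded as exclusive. That is fair as far as contradiction goes. But the article does state a covariate set, repeats the same five items in Table 1 and names unadjusted tests. Followed as written, ROM and MBI are compared without regard to motor stage.

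Four stronger readings are tempting, and the documents do not support them.

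- *That imbalance is likely.* Every probability above is below one half.
- *That the trial would report a false effect.* Chance imbalance can favour either arm, and the unadjusted test allows for it on average. The inflated error rates hold only given an imbalance that has occurred.
- *That imbalance would be invisible.* Table 1 is titled "Baseline assessment and sequence of trial measurements for primary and secondary outcomes". It is an assessment schedule, not a shell for the results paper, and it also omits the MMSE score needed for entry. Stage could still be tabulated under the CONSORT reporting that the Introduction promises. Baseline ROM and MBI would also show part of any imbalance, although neither replaces stage: MBI reflects overall independence, and ROM can be limited by pain as well as by weakness.
- *That adjustment is worth 25% to 67% more patients.* Those figures are 1/(1 − R²) at R² = 0.2 and 0.4. They ignore what baseline ROM or MBI would already explain.

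It also stands that adding stage to a list achieves no adjustment without a model that uses it. Two further uncertainties remain: the entry criterion refers to the affected limb without specifying the arm, and the article does not say whether ROM is active or passive. Both leave the strength of the link between stage and outcome open.

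**Conclusion.** The point holds in a limited form. Stage is required at entry, absent from the covariates and the baseline block, not stratified on and not adjusted for. With 24 per arm, a gap of 4 or more stage II-III patients has a probability of about 39% if half the patients are in those stages, and 24% to 34% under the two other splits tried. A gap of 6 or more has a probability of 15%, or 8% to 11%. These rest on an assumed distribution of stage.

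The consequence is lost precision and harder interpretation of ROM and MBI, not an invalid test. The primary VAS comparison is less affected. The precision gain from adding stage to a model that already holds the baseline outcome is unknown and may be well below 11% to 23% of the standard error. No stated figure in the article is wrong on this account. It is an inexpensive improvement to the analysis of secondary outcomes, and it is credible only if fixed before results are seen.

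**What to change.** 1. Add Brunnstrom stage as a row in the baseline block of Table 1 and to the covariates named in the Study design overview.
2. In the Data analysis section, replace the unadjusted between-arm test for ROM and MBI with a prespecified ANCOVA, or an equivalent model, that includes the baseline value of the outcome and Brunnstrom stage. Fix the coding of stage in advance, for example II-III versus IV-V.

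Both changes are needed, since the first alone adjusts nothing.

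Cost: one table row filled from a value already obtained at screening, and one degree of freedom for stage in two-level form (three if all four stages are kept as categories), besides the one for the baseline outcome. N stays 48 and no new assessment is required.
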